### Secondary objectives

The analysis of the impact on the patients’ functional status as measured by EEG, socioeconomical and psychosocial markers, and quality of life, will be considered as secondary outcomes.

Four secondary objectives are (i) Describe the subgroup profiles as a function of NDDs related symptoms intensity, potential comorbidities and neuropsychological performances; (ii) Compare feasibility of the multimodality biometry e-measurements vs. current measurements of neurodevelopment; (iii) Determine factors associated with level of disclosure of symptoms related to neurodevelopmental and mental health; (iv) Validate the clinical relevance of multimodality biometrics using mobile electroencephalography (EEG); (v) Determine multimodality biometric e-assessment as a monitoring tool.

### Research questions and hypotheses

Combining cognition, emotion, behavioral, and brain measurements at once through an unmodified tablet is a novel approach that could facilitate NDD evaluation in real-life practice at large scale. Overall, we hypothesize that brain functioning e-screening with XAI4Kids® in real life practice, will be as or more feasible and capable of capturing the heterogeneity of NDDs in the population, and ultimately serve as a first instance transdiagnostic evaluation for NDDs.

## Methods

The study was designed to examine whether multimodality biometry markers can reflect brain functioning as measured by cognitive, emotional, and/or behavioral performances in children aged 7 to 12 years using an unmodified tablet.

### Ethics approval

The EPIDIA4Kids study was approved by the Committee for the Protection of Individuals Sud-Est II (National French Register under the number 2022-A00766-37), the Commission Nationale de l’Informatique et des Libertés (CNIL) and was registered in October 2022 on ClinicalTrials.gov under the number (NCT05577533).

### Study design

EPIDIA4Kids is an observational uncontrolled multi-center study (several cities in France) during which no treatment or placebo will be administered. Complementing children’s assessment at baseline (T0), a subsample of 10% of the participants will be re-assessed after 2 months (end-T2). At least one of the parent or legal representatives and children will also answer questionnaires and will be interviewed using a semi-structured instrument (Figure 1).

### Aims of the study

The primary aim is to create a brain functioning normative database relying on digital epidemiology in children aged 7 to 12 years using multimodality biometry. Brain functioning will be analyzed as variations of three dimensions related to cognition, emotion, behavior, and their respective deviation related to NDDs symptoms (Table 1).

The secondary aims are defined as following:

▪ To identify subgroup profiles as a function of (1) NDDs related symptoms intensity, (2) pattern of psychiatric comorbidities, (3) neuropsychological results.▪ To compare feasibility of the multimodality biometry e-measurements to current screening measurements.▪ To validate the clinical relevance of multimodality biometrics using mobile electroencephalography (EEG).▪ To determine factors associated with level of disclosure of symptoms related to neurodevelopmental and mental health.▪ To determine multimodality biometric e-assessment as a monitoring tool.

### Participant

The inclusion criteria will be: (i) boys or girls of any ethnicity, aged 7–12 years (typically developing and diagnosed with NDDs); (ii) French native speakers; (iii) normal hearings, normal or corrected-normal vision; (iv) no brain trauma; (v) an estimated intelligence quotient of 85 and above (exclusion if score < 25th percentile) based on Weschler’s subtests Matrix Reasoning and Similarities (50); (vi) no history of co-morbid psychiatric illness that might confound the analysis of the study (e.g., schizophrenia, obsessive-compulsive disorder, major depression, or bipolar disorder); (vii) ADHD medications and Selective serotonin reuptake inhibitors (SSRIs) are not exclusionary since use of these medications is associated with neurodevelopmental disorder condition, but the treatment will be suspended 2 days before any cognitive evaluation.

The exclusion criteria will be: (i) failure to meet the inclusion criteria; (ii) lack of written informed consent: the child and at least one of the parents (or the legal representative) must sign the informed consent form.

### Recruitment

Recruitment procedures will be similar across sites, and trained staff will use a standardized script to determine eligibility in study participation. Participants (child and parent/legal representative) will be recruited from the local community, outpatient’s clinics, or referrals from physicians by advertising or interception method. They will complete the consent electronically and receive the automatically generated copy via email (Figure 1). The research assistants will be available to answer questions about study participation and tablet logistics. EPIDIA4Kids will ensure full time recruitment, to include a larger number of participants, as well as participants from a variety of social, geographic, and ethnic backgrounds, thereby increasing the accuracy and “generalizability” of the data collected as approved by the Comité de Protection des Personnes (CPP). Recruitment will be monitored across sites and, as recruitment proceeds, adjustments will be made to ensure that sociodemographic targets are reached. Once the compliance with the inclusion and exclusion criteria of the study is verified, the informed consent will be obtained, and baseline evaluation will be processed. The study will start in March 2023 and is expected to end in December 2024. Four hundred participants are targeted to complete the study.

**Figure 2 fig2:**
[figure not shown]
The EPIDIA4kIDS proposed framework. We will collect data from varied sources, including participant information with questionnaires and semi-structured interviews regarding their background, demographics, and medical history. Using unmodified tablet, we will gather data from video, digit-tracking, and EEG (for a sub cohort) as time-series logs. Based on various performance metrics, relevant features will be extracted automatically using various machine and deep learning algorithms to create a store of features clinically relevant based on the literature. Relevant features will be then processed and selected through statistical analysis and model selection that combined model training and model serving. Afterwards, analysis is performed to validate the relevance of the selected metrics for identification of cognitive, behavioral, and emotional states related to NDDs. EEG, Electroencephalogram; PCA, Principal Component Analysis; ADHD, Attention Deficit Hyperactivity Disorder; ASQ, Autism Spectrum Disorder; SLD, Specific Learning Disorders; DMD, Developmental Motricity Disorder; ROC, Receiver Operating Characteristic.

### Questionnaires and neuro-assessments

All questionnaires and neuro-assessments are summarized in Table 4. At baseline and T2-end, the visit will be conducted in a sequential manner with breaks. First, children will perform neuropsychological assessments through digitalized or paper/pencil WISC-V battery [1.5 h, (50)] with the Similarities, Vocabulary, Coding, Symbol search, Block design, Digit, Matrix reasoning subtests. Secondly, questionnaires will be answered digitally for:

▪ Demographic information (age, gender, language spoken, family structure, school, previous diagnosis for neurodevelopmental disorder) and scoring of manual laterality [Edinburgh handedness, short version, 4 items (54), estimated intellectual quotient (50), and sleep quality (Pittsburgh Sleep Quality Index, 11 items) (55)].▪ The French version of the ADHD-Rating Scale (56) incorporating the 18 criteria rating Inattention (sum of odd items scores) and Hyperactivity-Impulsivity (sum of even items scores) symptoms.▪ The French version of the Children Behavior Check List [short version, 32 items, (57) and Conners-3 (58)—psychopathological behavioral or emotional traits].▪ The Autism Quotient List French version scoring [10 items, (59)]—psychopathological behavioral or emotional traits.▪ The Developmental Coordination Disorder Questionnaire [DCDQ, 15 items, (60)].▪ The Behavioral assessment of executive function scoring [BRIEF, 72 items, (61)].▪ The French versions of the School Motivation Questionnaire [SMQ, 44 items, (62)] and the Grit-Scale for Children and Adult [GSCA, 12 items, (63)].

**Table 4 tab4:** Explanatory variables for the XAI4Kids^®^ e-measurement tool.

Neuropsychologic tests	Variables
	Reaction time: average reaction time (RT) for every executed task
	Hits: number of correct answers
	Total errors: total number of errors
	Wrong answers: number of answers that are not omission, perseverance and outliers
	Omission: reaction time = 0 ms
	Distractors: number of answers looking similar to the target answer
	Persévérance: 0 ms < reaction time < 100 ms
	Outliers: standard deviation of reaction time (exécution) < 3 x standard deviation (si RT≠0)
	Hits RT: median of reaction time for correct answers
	Hits RT SE: standard error de Hits RT
	SE variability: standard deviation of the 3 standard errors calculated for each task block (mesure of the participant variability)
	Hits rt block change: slope change for RT between blocks (vigilance)
	Hits SE block change: slope change for standard errors of RT between blocks (consistency and vigilance measure)
	Hits correct answers: Combination order of correct answers (behavioural trajectory measure)
	Hits correct answers through realization time: Combination order of correct answers (behavioural trajectory measure) by reaction time (speed processing measure)
	Distance deviation to stimuli: graphological fine motor skills
	Emotion analysis after stimuli: emotional control
	Attentional network: gap between medians of reaction time when the answer is correct or when it is wrong.
	Alerting: RTsans cue – RTdouble cue
	Orienting: RTcue centrale – RTorienting cue
	Conflict: RTflanker incongruent – RTflanker congruent
Video-tracking	Emotion, attention, social interaction: postural stability (51)
	Attention, information processing (semantic access, learning disability): fixation (amplitude, direction, interval time)
Digit-tracking	Attention, motricity: contact point (52)
	Real-time track (exploration time, direction, cumulative distance)
Eye-tracking	Attention, coordination: pro/anti-saccades (amplitude, direction, reaction time) (53)
	Attention, social interaction, information processing (semantic access, learning disability): fixation (amplitude, direction, interval time)
	Attention/stress: blink rate, pupil size, near point convergence

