**Methods and analysis:**

The EPIDIA4Kids is an uncontrolled open-label study. 786 participants will be recruited and enrolled if eligible: they are (1) aged 7 to 12 years and (2) are French speaker/reader; (3) have no severe intellectual deficiencies. Legal representative and children will complete online demographic, psychosocial and health assessments. During the same visit, children will perform additionally a paper/pencil neuro-assessments followed by a 30-min gamified assessment on a touch-screen tablet. Multi-stream data including questionnaires, video, audio, digit-tracking, will be collected, and the resulting multimodality biometrics will be generated using machine- and deep-learning algorithms. The trial will start in March 2023 and is expected to end by December 2024.

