There is a clear need for a rigorous evaluation of the feasibility, acceptability, and psychometric performance of e-screening for large scale children and adolescent cohort. A key consideration for evaluation is to determine whether gamified e-screening delivered through an unmodified tablet are valid and reliable for use compared to well-established assessment tools. For example, it has been shown that some tools have different psychometric properties when delivered online, suggesting a need for different cutoff points (35).

Taken together, the need to identify screening and assessment tools that are acceptable to both children and health professionals, overcome barriers to accessibility-to-care, to implementation into routine care, and are cost-effective and clinically useful, is crucially needed.

Today, billions of people are increasingly generating and collecting health-related data online (36) or on mobile devices. The opportunities for more accurate and effective health services are enormous (37, 38). Digital epidemiology uses the new and rapidly expanding digital data streams from mobile devices to advance public and personalized health (39, 40). These datasets are then used by artificial intelligence algorithms to improve our understanding of health and disorders dynamics, both in individuals and in the general population. In natural environment, digital epidemiology represents a new approach that aims at measuring human behavior and may, combined with clinical (endo)phenotypes, enhance capability and sensitivity in early identification, diagnosis, and management of health conditions. Moreover, such a combined approach may easily allow clinicians to perform a more personalized and patient-tailored diagnostic and therapeutic approach.

As children and adolescents are so familiar with digital technologies (41, 42), building the right services specifically designed and dedicated to them will help to prevent, monitor, and intervene more appropriately on neurodevelopmental and related mental disorders at a larger scale.

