Here, we investigate how digital phenotyping integrated with clinical (endo)phenotypes constitutes a new method for building comprehensive datasets based on digital epidemiology to create meaningful metrics of cognition, emotions, and behavior specific to children and adolescents. These detectable and measurable features will help understanding better brain development and hereby identifying prominent predictive variables to achieve dimensionality reduction and risk factors for NDDs.

**Purpose** (Table 1)—the EPIDAI4Kids study will examine brain functioning in children aged 7 to 12 years using biometrics and digital biomarkers to create meaningful metrics of cognition, emotions, and behavior specific to children and adolescents, while they are playing at gamified assessments on an unmodified tablet.

**Table 1 tab1:** Primary and secondary objectives, research questions, and hypotheses.

Primary objective	Research question	Outcome	Measures	Testable hypothesis
To create and compare a normative base of brain functioning in children aged 7 to 12 years using multimodality biometry e-measurements vs. paper-based screening	Is the neuro-developmental e-assessments as or more acceptable to children and health practitioners than paper-based screening?	Acceptability: % children in the study failing finishing the e-assessments	Acceptability	Higher proportion of children and health practitioners will affirmatively respond to acceptability for the e-measurement
		% of participants reporting that e-questions and psychometric games are easy to navigate around on the tablet	Qualitative; semi-structured interview	
			Quantitative: proportion of participants feeling uncomfortable	
To compare psychometric properties (sensitivity, specificity, cutoff points) of paper-based screening vs. the psychometric games?	What are the performances in cognition, emotion and/or behavior in children aged 7 to 12 years on child neurodevelopment?	Efficiency: correlations between scoring of paper-based screening performances and biometrics within each participant and inter-examinator	Quantitative: video and audio will be recorded for about 30 min while the children are playing on a unmodified tablet. Eye-, face- digit- and sound- will be extracted from recorded video by ML/DL algorithms.	Strong correlations between paper-based screening performances (psychometric properties) and multimodality biometrics within each participant.

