				Less variability inter-examinator on e-assessments than on paper-based screening
Secondary objective	Research question	Outcome	Measures	Testable hypothesis
To compare feasibility of the multimodality biometry e-measurements?	Is the neuro-developmental e-assessments as or more feasible to children and health practitioners than paper-based screening?	Feasibility: % children in the study failing finishing the e-assessments	Qualitative: semi-structured interviews	Higher proportion of children and health practitioners will affirmatively respond to feasibility for the e-measurement
		% of health practitioners reporting that e-questionnaires and psychometric games are easy to navigate around on the tablet		
To validate the clinical relevance of multimodality biometrics	Are multimodal biometry e-measurements clinically relevant metrics for neurodevelopmental and mental health?	Match mobile EEG biomarkers for neurodevelopmental and mental health with multimodality biometrics	Quantitative: electroencephalographic (EEG) biomarkers of cognitive, emotional, and behavioral performance in children aged 7–12 years	Compare EEG signals obtained while children are playing with biometrics measurements related to well-characterized EEG signatures for related mental health in children (P2, N170, P300 amplitude and latence, Ratio Theta/Beta (TBR), Frontal Theta and Delta Power, Posterior Alpha et beta Power)
To determine factors associated with level of disclosure of symptoms related to neurodevelopmental and mental health	What factors are associated with risk of neurodevelopmental and mental health?	Identification of factors that significantly increase odds of neurodevelopmental and mental health reported symptoms	Quantitative: (1) demographic variables (age, gender, SES), (2) medical status (current NDD status, history), (3) psychopathological scores and quality of life (BRIEF, CBCL, ADHD scale, ASQ-10, PSQI, Grit questionnaire, SMQ)	Compared to paper-based screening, e-screening promotes greater disclosure
To determine multimodality biometric e-assessment as a monitoring tool		Examination of significant changes of either or both scores compared with baseline (repeated testing)	Quantitative: compared 4-month follow-up scores of e-assessment and paper-based screening with those obtained at baseline	More variability of scoring in those obtained from paper-based screening will be expected than those from e-assessment

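### The WISC-V comparator may be digital or on paper, which contradicts the paper-based comparator named in the abstract and the primary objective

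*Protocol article*

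**What the plan says.** The protocol article describes the mode of the conventional testing in three places.

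- **Questionnaires and neuro-assessments (methods).** For both baseline and T2-end, "children will perform neuropsychological assessments through digitalized or paper/pencil WISC-V battery". No rule says which child, site or visit gets which form. The same section has the questionnaires answered digitally.
- **Abstract, Methods and analysis.** Here "children will perform additionally a paper/pencil neuro-assessments followed by a 30-min gamified assessment on a touch-screen tablet". No digital form is mentioned.
- **Table 1.** The primary objective is a normative base "using multimodality biometry e-measurements vs. paper-based screening". The next objective is "To compare psychometric properties (sensitivity, specificity, cutoff points) of paper-based screening vs. the psychometric games". The attached hypotheses are "Strong correlations between paper-based screening performances (psychometric properties) and multimodality biometrics within each participant" and "Less variability inter-examinator on e-assessments than on paper-based screening".

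Table 3 makes WISC-V subtests the main convergent measures for the cognitive domains, so the mode of the WISC-V largely determines what the cognitive comparator is.

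On whether mode matters, the Introduction says that "some tools have different psychometric properties when delivered online, suggesting a need for different cutoff points".

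The section on the hypothesis testing framework gives site and devices as examples of nesting levels and age and gender as covariates, and leaves other background variables open. WISC-V mode is not named there.

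**The concern.** The methods section permits a comparator that the abstract and the primary objective exclude. For a child tested on the digital WISC-V there is no paper cognitive score, so that child does not contribute to an e-versus-paper cognitive comparison, whatever the result is called.

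The Introduction treats delivery mode as a reason why psychometric properties and cutoffs may differ, and the plan then lets the reference test vary in that respect. If the two forms differ in level, a single cutoff or reference interval taken from the mixture describes neither form. If examiners differ in the form they use, the difference adds to the between-examiner variance on the side labelled paper. If a retested child changes form, the change appears as instability of the paper score. These last two effects bear on hypotheses that expect the conventional side to be the more variable one, so a mode difference could help confirm them without the tablet tool being any better.

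**Working it through.** The plan states no figure on this point, so there is none to reproduce. The contradiction comes from the text. The arithmetic below only shows how large the consequence could be, under assumptions.

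**Texts side by side.** Abstract: paper and pencil. Table 1: paper-based. Methods: digital or paper and pencil, at both visits. The three cannot all describe the same comparator.

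**Inputs.** From the documents: 400 children targeted to complete (Recruitment; Sampling). Assumed, because the documents do not give them: a level difference d between forms of 0.2 to 0.4 SD, a digital share p = 0.5, and a cutoff at -1 SD of a normal score.

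**1. Share below the cutoff.** In the unshifted form the share is Φ(-1) = 15.9%. In the shifted form it is Φ(-1 ± d):

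| d (SD) | Scores shifted up | Scores shifted down |
|---|---|---|
| 0.2 | Φ(-1.2) = 11.5% | Φ(-0.8) = 21.2% |
| 0.4 | Φ(-1.4) = 8.1% | Φ(-0.6) = 27.4% |

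These figures apply only to children tested in the shifted form. Over all children at p = 0.5 the share is the average with 15.9%:

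- Shifted up: (15.9 + 11.5)/2 = 13.7% and (15.9 + 8.1)/2 = 12.0%.
- Shifted down: (15.9 + 21.2)/2 = 18.5% and (15.9 + 27.4)/2 = 21.6%.

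**2. Between-examiner variance on the conventional side.** If half the examiners use each form, the form adds p(1-p)d² = 0.25d²:

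- d = 0.2: 0.25 × 0.04 = 0.010 SD².
- d = 0.4: 0.25 × 0.16 = 0.040 SD².

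Against an assumed true examiner variance of 0.05 SD², the apparent variance is inflated by (0.05 + 0.010)/0.05 = 1.20 to (0.05 + 0.040)/0.05 = 1.80. If all examiners use the forms in the same proportions, the average form effect is the same for each examiner and this term vanishes.

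**3. Retest.** A child who changes form between visits shows a spurious change of d. The Study design section puts the retest subsample at 10%, or 0.10 × 400 = 40 children (the Figure 1 caption gives a different count). In a group that small, a few such children could matter.

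**4. Correlation.** Two simple mechanisms pull in opposite directions.

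- A level shift unrelated to the game score lowers the correlation by the factor 1/√(1 + p(1-p)d²). From an assumed 0.70 it becomes 0.70/√1.01 = 0.697 at d = 0.2 and 0.70/√1.04 = 0.686 at d = 0.4.
- Shared digital-method variance m added to both scores raises it. From an assumed 0.50 it becomes (0.50 + m)/(1 + m), which is 0.55/1.05 = 0.52 at m = 0.05 and 0.65/1.15 = 0.57 at m = 0.15 in digitally tested children. Averaged with 0.50 at p = 0.5, this is 0.51 to 0.53.

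For scale, the approximate 95% half-width for a correlation of 0.50 in 400 children is 1.96 × (1 - 0.50²)/√399 = 0.07. Both effects lie well inside it.

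**The case against.** **The label may be loose.** The Primary objective section describes the comparator as current convergent validity measures, and the aims speak of current screening measurements. On that reading, paper-based simply means conventional. This stands in part. Since the questionnaires are digital and several of them appear in Table 3, a paper WISC-V alone would not make the whole comparator paper-based. But the abstract does say paper and pencil, and Table 1 does claim results against paper, so the wording still needs reconciling.

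**A condensed article leaves such detail out.** Which site uses which form, and how it is recorded, could sit in the full protocol. That would answer an omission. Here the article addresses mode and does so inconsistently.

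**There is partial mitigation.** The nesting by site and devices is an open list of examples, further variables may be added, and the Discussion undertakes to limit hardware heterogeneity and to review examiner variance. It would be wrong to say that the model excludes mode. None of this fixes the WISC-V mode, however, and a site intercept does not repair a cutoff or a sensitivity estimate.

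**Stronger readings that the documents do not support.** A reader might infer that mode is aliased with site, that children will switch mode between visits, or that a shared digital medium inflates agreement in favour of the tool. No section links mode to site or says that a child may change form; these are possibilities left open. Nor does any section say what digitalized covers (display, response or scoring), so a medium shared with the games is an assumption. The direction of any effect on the correlations is open.

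**Conclusion.** The point holds as a contradiction about the comparator: digital or paper in the methods, paper in the abstract and in the primary objective and hypotheses. The plan's own premise that delivery mode can change cutoffs makes it more than a matter of wording.

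The results most exposed are cutoffs, sensitivity and specificity, reference intervals, inter-examiner variability and retest change. The correlations are probably little affected, in an uncertain direction.

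The size cannot be fixed from the documents. At an assumed shift of 0.2 to 0.4 SD, the flagged share moves by roughly 4 to 12 percentage points among children in the shifted form, and by roughly 2 to 6 points overall at an assumed even split. If the two forms are equivalent in level and precision, or only one is used in practice, the numerical effect disappears and only the wording remains to be corrected. Severity is moderate.

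**What to change.** - **Preferred.** Reconcile the abstract, Table 1 and the section on questionnaires and neuro-assessments by naming one WISC-V mode for all sites and both visits.
- **If one mode is not practicable.** Record the mode per child and visit, and keep it constant for each child between baseline and T2-end. Report the WISC-V comparisons stratified by, or adjusted for, mode. Let only paper-tested children support a claim against paper.
- **Wording.** Keep the term paper-based for measures actually given on paper, and call the digitally answered questionnaires and any digital WISC-V conventional measures.

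The cost is a short text change and, under the second option, one data field. Sites equipped for the digital form lose some flexibility, or fewer children enter the paper comparison. At an assumed even split, that comparison would rest on 0.5 × 400 = 200 children.

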#### The multimodality biometry tool description

The XAI4Kids® Multimodality Biometry tool has been developed by O-Kidia, SAS, and is composed of several technological components (Tables 2
3):

▪ The unmodified tablet: data will be collected in ecological context during the session to minimize stigma. Participant’s main biometry parameters (e.g., eye-, face-, and digit-tracking, frequencies, etc.), clicking, taping, and video from the intrinsic camera will be recorded to reflect of the child’s performances.▪ The O-Games: a series of gamified psychometric sessions, which will engage the participants to perform as the best, and stimulate the cognitive, emotional, and behavioral functions of each participant. Games were developed for Android with Unity^1^ and will be installed on each participant’s table.

**Table 2 tab2:** Study workflow at baseline.

Name	Description	Time	Who	Visit
Screening worksheet	Eligibility criteria	10 min	Y, P	B
Modified Ohio State TBI Screen-Short Ver	TBI rule-outs at BL; TBI	5 min	P	B
Demographics domain	demographics, race, gender, family structure, SES	20 min	P	B
Medications	Medical history, medications	5 min	P	B
Pittsburgh Sleep Quality Index	Sleep habits	5 min	P	B, T2-end
Children’s Sleep Habits Questionnaire	Sleep habits	5 min	Y	B, T2-end
Questionnaires for parent	ADHD-rating scale, Children Behavior Check, BRIEF, DCDQ, Conners 3	20 min	P	B, T2-end
Questionnaires for child	ADHD-rating scale, ASQ-scale, Grit scale, and SMQ	20 min	Y	B, T2-end
WISC-V (substest)	7 subtests Symbol, Cubes, Code, Comprehension, Letter-Number sequences, matrix, and similitude	45 min	Y	B, T2-end
O-Games battery	5 psychometric games	20–35 min	Y	B, T2-end
Breaks	As much as needed	20 min	Y	B, T2-end

**Table 3 tab3:** Convergent validity measures for the XAI4Kids^®^ e-measurement tool.

What it measures	Stream data type	Convergent validity measures
Visio-spatial processing	Rocket	WISC-V, block design
	SES4ME	WISC-V, symbol search
	O-TOM	WISC-V, barrage
Working memory	Untangle, EEG (P3b)	WISC-V, letter-number sequences
Episodic memory	O-G	WISC-V, letter-number sequences, digit-span
Attention	Rocket, connect	WISC-V, digit span, coding, symbol search
Speed processing	Connect	WISC-V, symbol search (immediate recall) coding
Language	O-KIDO	WISC-V, comprehension, vocabulary,
Executive functions	O-MAZE	WISC-V, BRIEF, vocabulary,
Auditive Attention	O-METRO	WISC-V, digit span
Anxiety	EEG and video-analysis	CBCL subtest
Sleep	EEG and video-analysis	PSQI

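### The two WISC-V subtest lists disagree and neither covers the Table 3 comparators: under either list two Table 3 rows, and one game entirely, have no convergent-validity measure

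*Protocol article*

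**What the plan says.** Three places in the protocol article bear on which WISC-V subtests a child takes.

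- **Table 2 (workflow)** schedules "7 subtests Symbol, Cubes, Code, Comprehension, Letter-Number sequences, matrix, and similitude" at baseline and at the end-T2 visit, with 45 min allotted. It describes the game battery as "5 psychometric games".
- **Questionnaires and neuro-assessments** covers the same two visits. It describes a "digitalized or paper/pencil WISC-V battery [1.5 h, (50)]" and lists its contents as "with the Similarities, Vocabulary, Coding, Symbol search, Block design, Digit, Matrix reasoning subtests".
- **Table 3 (convergent validity measures)** pairs each game or data stream with its comparator. Untangle (working memory) has "WISC-V, letter-number sequences"; O-G (episodic memory) has "WISC-V, letter-number sequences, digit-span"; Rocket and Connect (attention) have "WISC-V, digit span, coding, symbol search"; O-TOM in the visuo-spatial block has "WISC-V, barrage". O-METRO (auditory attention) has Digit Span alone.

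Table 1 lists, above the secondary objectives, an efficiency outcome based on correlating paper-test scores with the biometrics. The Primary objective section says the tool is judged against convergent validity measures, and Table 3 is where these are named.

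**The concern.** A correlation needs both scores. If a subtest that Table 3 relies on is not given at the visit, no later analysis plan can supply it. With two seven-subtest lists that differ, the reader cannot tell which paper scores will exist, and Table 3 appears to ask for scores that neither list provides. At stake are the convergent-validity claims for particular games. The end-T2 comparison of paper and tablet scores uses the same subtests and inherits the same ambiguity.

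**Working it through.** No sample-size or power formula applies; this is a comparison of lists. I read Cubes as Block Design, Code as Coding, Symbol as Symbol Search, similitude as Similarities, matrix as Matrix Reasoning and Digit as Digit Span. Without that reading the mismatch would be larger.

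The count of seven stated in Table 2 reproduces, and the text list also has seven.

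| Subtest | Table 2 | Text | Where Table 3 uses it |
|---|---|---|---|
| Block Design | yes | yes | Rocket, visuo-spatial (only comparator) |
| Symbol Search | yes | yes | SES4ME (only comparator); attention; speed; both eye-tracking rows |
| Coding | yes | yes | attention; speed; visual motricity |
| Matrix Reasoning | yes | yes | none (used for eligibility) |
| Similarities | yes | yes | none (used for eligibility) |
| Letter-Number | yes | no | Untangle (only comparator); O-G |
| Comprehension | yes | no | O-KIDO |
| Digit Span | no | yes | O-METRO (only comparator); O-G; attention |
| Vocabulary | no | yes | O-KIDO; O-MAZE (alongside BRIEF) |
| Barrage | no | no | O-TOM, visuo-spatial (only comparator) |

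**Overlap.** Five subtests are shared, two are only in Table 2 and two only in the text: 5 + 2 + 2 = 9 different subtests across both lists.

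**Coverage of Table 3.** Table 3 names eight WISC-V comparators (the ten rows above less Matrix Reasoning and Similarities).
- Table 2 covers 8 − 3 = 5; it lacks Barrage, Digit Span and Vocabulary.
- The text covers 8 − 3 = 5; it lacks Barrage, Letter-Number and Comprehension.
- Both lists together cover 8 − 1 = 7; only Barrage is missing.

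**Effect by row.**
- *Table 2 followed:* O-TOM visuo-spatial and O-METRO have no comparator. O-G keeps Letter-Number, attention keeps Coding and Symbol Search, O-KIDO keeps Comprehension, and O-MAZE keeps BRIEF.
- *Text followed:* O-TOM visuo-spatial and Untangle have no comparator. O-G keeps Digit Span and O-KIDO keeps Vocabulary. Attention and O-MAZE lose nothing.
- O-TOM also stands in the social-abilities row, where its comparators are a CBCL subtest and the ASQ, both collected. So it is not left without any measure.

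Games with no comparator in any row: one under Table 2 (O-METRO), one under the text (Untangle), none if all nine subtests are given.

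**Could something else in the article settle it?** The text refers to Table 4 as a summary, but Table 4 lists tablet-derived variables and no WISC-V subtests. Nor can Barrage be read as another name for Symbol Search or Coding, because Table 3 names those two separately.

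**Smallest sufficient list.** Block Design, Symbol Search, Letter-Number and Digit Span are each the only comparator for some row (4). Eligibility requires Matrix Reasoning and Similarities (2). O-KIDO requires Vocabulary or Comprehension (1). 4 + 2 + 1 = 7. Coding is not essential, because every row that names it also names Symbol Search. Keeping every named comparator except Barrage takes the seven covered comparators plus the two eligibility subtests: 7 + 2 = 9.

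**Related mismatches.** WISC-V time is 45 min in Table 2 and 1.5 h = 90 min in the text, a factor of two. Table 3 uses nine game names (Rocket, SES4ME, O-TOM, Untangle, O-G, Connect, O-KIDO, O-MAZE, O-METRO) against a battery of five.

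**The case against.** The strongest reply is that the primary outcome is not defined pair by pair. Table 1 speaks of correlations between paper performance and biometrics in general, and the Discussion describes models that combine many features, each resulting score being set against one or more questionnaires. Losing one game–subtest pair weakens one domain and does not stop the primary analysis. This stands, and it limits the reach of the point.

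A reader might infer that several games have no comparator at all. The documents do not support that: O-TOM keeps CBCL and ASQ, O-MAZE keeps BRIEF, and only one game is stranded under either list. Five games would lose a comparator only if just the five shared subtests were given, which neither place states. A reader might also infer that sites will follow different lists, so that fewer than 400 children contribute to some correlations. The study has several sites, but nothing says they use different lists, so this is conjecture.

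The count of five against nine games also needs care. The Table 3 column holds data streams such as EEG and eye-tracking as well as games, and the article does not say that each name is a separate game. It cannot be concluded that four games fall outside the battery, only that the battery is not identified.

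The reply that a journal article condenses a fuller protocol does not answer the point. Nothing is being asked for that was left out: two full lists are printed, and they conflict with each other and with Table 3.

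**Conclusion.** The point holds, with a bounded size. The article contradicts itself on the WISC-V schedule (five of seven subtests shared), and neither list satisfies Table 3 (five of eight comparators each). Under either list two Table 3 rows have no comparator: O-TOM visuo-spatial in both cases, plus O-METRO under Table 2 or Untangle under the text. One game is left with none anywhere. The correlations for those rows cannot be computed; the remaining game rows can be analysed, some with fewer comparators than named. It does not follow that the primary objective as a whole fails or that the sample shrinks.

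The conclusion rests on the subtest names being matched as described, and on a visit following one list or the other. If all nine subtests were given, only the Barrage row would remain without a comparator.

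**What to change.** Use one subtest list in Table 2, in Questionnaires and neuro-assessments, and in Table 3. There are two workable options.

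- **Seven subtests, the number already planned:** Matrix Reasoning, Similarities, Block Design, Symbol Search, Letter-Number, Digit Span, and Vocabulary or Comprehension. These serve eligibility and give every row except Barrage at least one comparator. The cost is losing Coding and one of Vocabulary or Comprehension as additional comparators. Choosing Vocabulary retains the WISC-V comparator for O-MAZE as well as O-KIDO; choosing Comprehension leaves O-MAZE with BRIEF alone.
- **Nine subtests:** the two lists combined. This keeps every named comparator except Barrage, at the cost of two more subtests per child per visit.

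Either schedule Barrage or remove it from Table 3. Make no convergent-validity claim for any row whose comparator is not given. Reconcile the WISC-V duration, and state which Table 3 names make up the five-game battery. With seven subtests and Barrage removed, this is a correction to the text and tables and adds no subtest to the visit.
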